## Protocol overview

3

### Study development and structure

3.1

The Delphi survey will be developed using the browser-based REDCap software, chosen for its ease of use, efficient distribution, and ability to maintain participant anonymity. The survey will be structured into five distinct parts:1.*Part 1*: Will collect participant demographic details (eg, age, location, and experience) to assist with quality assurance.2.*Part 2*: Will evaluate how experts identify parameters impacting surgical difficulty and risk factors. This section will aim to gather information on participants' experience and opinions regarding factors influencing surgical difficulty and peri- and postoperative complication risks, as well as their perspectives on the strengths, weaknesses, and applicability of existing perioperative risk prediction tools.3.*Part 3*: Will focus on expected/known (preoperative) non–organ-specific factors that impact surgical difficulty and complication risk, addressing how these factors contribute to perioperative risk estimation.4.*Part 4*: Will examine unexpected/unknown (intraoperative) non–organ-specific factors, organ-specific parameters affecting surgical difficulty and complication risk, and immediate postoperative conditions that may influence peri- and postoperative risk estimation.5.*Part 5*: Will collect participant identification and consent.

Each section will contribute distinct data, which will be elaborated upon further in the survey outline. For a comprehensive breakdown of the description, content, aims, and rationale behind the five parts of the Delphi survey, see Table 5. To ensure quality control, the questionnaire will be developed in collaboration with methodologists and reviewed by experienced urologists.

**Table 5 t0025:** Description, content, aims, and rationale of the five parts of the Delphi Survey

Part	Description	Content, aims, and rationale
1	Participant demographic details	Basic participant demographic information (eg, age, location, experience) to assist in quality assurance
2	How to identify parameters impacting surgical difficulty and risk factors	Information regarding gauging participant experience in opinions of potential factors impacting surgical difficulty and peri- and postoperative risk for complications; and opinion on the meaningfulness, strengths, and weaknesses of pre-existing perioperative risk prediction tools
3	Non–organ-specific factors impacting surgical difficulty and risk for complication	Achieving consensus on patient-specific characteristics and conditions that may affect the difficulty of surgery and risk stratification
3A	Expected/known (preoperative) non–organ-specific parameters	Defining preoperatively existing patient-specific parameters (eg, body mass index, ASA score, biological sex, prior abdominal surgery, diabetes)
3B	Unexpected/unknown (intraoperative) non–organ-specific parameters	Defining patient-specific parameters that occur unexpectedly or become apparent during the operation (eg, bleeding tendency or extensive adhesions)
3C	Unexpected/unknown (postoperative) conditions occurring prior to discharge or max within 24 h (eg, acute kidney injury quantified by GFR decrease [%])	Defining immediate postoperative parameters that might have an impact on morbidity and mortality (eg, acute kidney injury quantified by GFR decrease [ml/min])
4	Targeted organ-specific factors impacting surgical difficulty and risk for complication (organ-specific scoring systems)	Obtaining consensus on patient-specific characteristics and conditions that may affect the difficulty of surgery and risk stratification
4A	Expected/known (preoperative) targeted organ-specific parameters	Defining preoperatively existing targeted organ-specific parameters (eg, size and location of the tumour, anatomy and morphology of the organ)
4B	Unexpected/unknown (intraoperative) targeted organ-specific parameters	Defining patient-specific parameters that occur unexpectedly or become apparent during the operation (eg, fibrosed periprostatic tissue, cancer extension beyond the confines of the targeted organ)
5	Participant identification and consent	Requesting the full name, preferred title, and professional affiliations of each participant of the Delphi survey for quality assurance and further ensuring that participants are compensated for their time with PubMed listed collaborative authorship

ASA = American Society of Anesthesiologists; GFR = glomerular filtration rate.

### Assessment of risk and difficulty factors

3.2

Risk factors affecting surgeon performance will be rated exclusively by surgeons, whereas those impacting the anaesthetist will be assessed solely by anaesthetists. Risk factors influencing both surgical and anaesthetic outcomes will be evaluated by both groups. Surgeons will assess parameters related to surgical difficulty and complication risk, while anaesthetists will focus on factors contributing to the risk of complications.

To enhance accessibility, the risk prediction index will primarily utilise routinely available preoperative patient characteristics and easily quantifiable intraoperative conditions. Each variable will be assigned a numerical value, with higher values indicating greater significance in determining outcomes.

As peri- and postoperative complications arise from both surgical and anaesthetic risk factors, input from both disciplines will be essential in developing the index.

To evaluate the association between proposed parameters and complications, and to estimate their likelihood, a nomogram will be constructed using data from the CAMUS Collaboration database, supplemented with parameters from a prospective open cystectomy database at the University of Bern. The likelihood of complications will be critical, as each parameter will be assigned a specific weight to be incorporated into the risk prediction score.

Institutional databases will be utilised to create a model predicting the impact of certain parameters on peri- and postoperative complications at 90 and 360 d after surgery. Additionally, organ-specific scoring systems for bladder, prostate, kidney, and testicular cancer will be developed using a nomogram and institutional databases.

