**Table 2 t0010:** Proposed CAMUS intra- and postoperative risk and difficulty estimation indices (IPRADES)

CAMUS IPRADES indices								
Non–organ-specific factors impacting surgical difficulty and risk for complication								
No.	Expected/known (preoperative) parameters				Unexpected/unknown (intraoperative) parameters			
	Parameter	Surgeon		Anaesthetist	Parameter	Surgeon		Anaesthetist
		Surgical difficulty (0 = no, 1 = yes)	Risk for complication (0 = no, 1 = yes)	Risk of complication (0 = no, 1 = yes)		Surgical difficulty (0 = no, 1 = yes)	Risk for complication (0 = no, 1 = yes)	Risk of complication (0 = no, 1 = yes)
1	Diabetes				Intraoperative fluids administered (ml)			
2	ASA classification				Estimated blood loss (ml)			
3	Timing of surgery (AM, PM)				Duration of operation (min)			
4	BMI (kg/m^2^)				ECG abnormalities			
5	Anticoagulant agents				Ventilation difficulties			
6	Elective vs emergency				General overall tissue quality			
7	Previous therapy: non–organ-specific (eg, radiation)				Ooziness/tissue vascularity			
8	Charlson Comorbidity Index				Scarred tissue			
9	Prior abdominal surgical history + type of surgery (eg, bowel resection vs cholecystectomy)				Adherent tissue			
10	Nutrition status (eg, albumin, weight loss, cachexia)				Identifiable planes			
11	Age				Vision			
12	Gender				Vessel injury			
13	Steroid use for chronic condition				Intraoperative blood transfusion			
14	Smoking status				–			
15	Further parameters to be proposed by Delphi experts				Further parameters to be proposed by Delphi experts			
Unexpected/unknown (immediate postoperative) parameters								

Parameter		Surgeon				Anaesthetist		
		Risk for complication (0 = no, 1 = yes)				Risk of complication (0 = no, 1 = yes)		

Acute kidney injury (ie, eGFR decrease by 10 ml/min)								
Significant demand for analgesia (ie, opioids >50 μg)								
Targeted organ-specific factors impacting surgical difficulty and risk for complication (organ-specific scoring system) shown in an exemplary way for laparoscopic/robotic radical prostatectomy								
	Expected/known (preoperative) parameters				Unexpected/unknown (intraoperative) parameters			
	Parameter	Surgeon			Parameter	Surgeon		
		Surgical difficulty (0 = no, 1 = yes)	Risk for complication 0 = no, 1 = yes)			Surgical difficulty (0 = no, 1 = yes)	Risk for complication (0 = no, 1 = yes)	
1	Prostatic size (cc) on MRI (eg, very small or very large)				Narrow bony pelvis			

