### Study aims

2.2

The final Delphi document will aim to synthesise expert consensus and provide guidance in areas of on-going debate within the field of urological surgery. Its findings will be of significant relevance and potential applicability to other surgical disciplines, ensuring the dissemination of optimised guidance to clinicians and patients alike. Ultimately, these position statements will be incorporated into internationally recognised guidelines issued by urological associations.

The primary objective of this study will be to develop a peri- and intraoperative risk prediction index and scoring system to estimate and quantify surgical difficulty, as well as to construct targeted, organ-specific scoring systems based on pre- and intraoperative factors. Similar to the existing renal scoring systems [8,9,11], the objective will be to establish a checklist-based framework to assist in surgical planning, case selection, and stratification of procedures based on their suitability for teaching purposes (see Fig. 1B).

The main objectives of the study will be the following (Table 4):1.To predict intraoperative (during intervention), perioperative (in-hospital period), and postoperative (within a defined period after intervention) outcomes by considering both pre- and intraoperative factors2.To predict intra-, peri-, and postoperative outcomes based solely on preoperative factors, thereby optimising resource allocation and enabling the identification of appropriate teaching cases prior to surgery3.To define surgical difficulty as an independent metric for the comparative analysis of intra-, peri-, and postoperative outcomes across surgeons and procedures. This will necessitate the delineation of parameters contributing to surgical complexity from both an anaesthetic and a surgical perspective. Consideration will be given to anaesthetic and surgical case volume, frequency of procedures over a given timeframe, and individual learning curves, as these factors will influence both case complexity and the risk of complications4.To develop multiple indices for surgical risk and difficulty estimation, which will be calculated both preoperatively and immediately postoperatively

**Table 4 t0020:** Study aims

#	Aim
1	To predict intra-, peri-, and postoperative outcomes by considering pre- and intraoperative factors

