2	To predict intra-, peri-, and postoperative outcomes by considering preoperative factors only, to optimise the allocation of critical care resources or defining teaching-appropriate cases before surgery starts
3	To determine surgical difficulty as a separate matter to judge surgical performance by improving the comparison of intra- and postoperative outcomes between surgeons and between different interventions
4	To define parameters that make certain operations (and approaches) for anaesthetists and urologists more difficult
5	To create several indices (surgical risk and difficulty estimation) that are calculated before and immediately after surgery

The surgical difficulty and risk estimation tool will integrate five categories of patient-specific parameters (Table 2):1.Preoperative (known, expected) patient-specific characteristics and conditions (eg, body mass index [BMI], ASA score, sex, prior abdominal surgery, and comorbidities)2.Intraoperative (unknown or unexpected) body/patient-specific characteristics and conditions (eg, bleeding tendency, restricted operative space due to a narrow bony pelvis, or extensive adhesions)3.Preoperative targeted organ-specific parameters (eg, tumour size and location, organ anatomy and morphology, or a history of prior interventions on the targeted organ such as biopsies or transurethral resection of the prostate preceding prostatectomy)4.Intraoperative targeted organ-specific parameters (eg, fibrosed periprostatic tissue or tumour extension beyond the targeted organ).5.Unexpected/unknown postoperative conditions prior to discharge or within 24 h (eg, acute kidney injury, quantified by a decrease in glomerular filtration rate [ml/min])

Surgical and anaesthetic parameters will be evaluated independently to account for the influence of case volume and individual learning curves on surgical complexity and risk. The key variables will include the total case volume, frequency of procedures performed within a defined period, and complexity of prior cases. Additionally, institutional case load will be considered when estimating perioperative morbidity risk (eg, in tertiary referral centres).

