Logistic regression will be used to examine the relationship between major complications/death, and the risk index score (treated as an ordered categorical variable based on predefined categories) and its components across the three patient cohorts. Model discrimination will be assessed by calculating c-statistics (area under the receiver operating characteristic curve). For model calibration, the Hosmer-Lemeshow (HL) goodness-of-fit test will be used to compare predicted versus observed outcomes between the two cystectomy cohorts. In the final cohort, differences in complication rates across individual scores will be compared using chi-square tests. Additionally, using morbidity (complicated/uncomplicated) and mortality (dead/alive) as dichotomous dependent variables, multiple logistic regression models will be derived. Overall model significance will be assessed via the model chi-square statistic, and differences between observed and expected outcomes will be evaluated using the HL test.

To develop the surgical difficulty index, pre-, intra-, and postoperative parameters and outcome measures will be determined by experienced high-volume surgeons (≥1000 major interventions and >10 yr of surgical experience) using the Delphi method. Pre- and perioperative parameters that potentially increase operative difficulty and risk will be assessed using a 5-point scale, as shown in Supplementary Tables 1–3. Primary outcome measures for surgical difficulty will include operation duration, blood loss and transfusion, use of haemostatic agents, and the surgeon’s judgement (on a scale from 0 to 100).

The performance of the universal surgical risk calculator, which includes multiple specialities and hundreds of procedures, will be compared with the performance of our risk calculators, specifically programmed for this score development. This comparison will be made for individual procedures (eg, RC and RP).

Alternatively, to create risk prediction models, random-intercept, fixed-slope hierarchical models (using SAS GLIMMIX) will be employed. These models account for case clustering within hospitals and impose an empirical Bayes-type shrinkage adjustment. As a result, both universal and procedure-specific surgical risk calculators will be developed. The performance of the universal versus procedure-specific models will be evaluated using three metrics: the c-statistic, the HL statistic (in a revised graphical form), and the Brier score.

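### Anaesthetic difficulty is a stated aim, but anaesthetists rate only complication risk and the protocol names no anaesthetic difficulty outcome

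*Protocol article*

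**What the plan says.** **The aims.** Aim 4 in Table 4 reads "To define parameters that make certain operations (and approaches) for anaesthetists and urologists more difficult". Objective 3 in section 2.2 sets out to define surgical difficulty as a metric in its own right and adds: "This will necessitate the delineation of parameters contributing to surgical complexity from both an anaesthetic and a surgical perspective".

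**The rating instrument.** Section 3.2 divides the work between the disciplines: "Surgeons will assess parameters related to surgical difficulty and complication risk, while anaesthetists will focus on factors contributing to the risk of complications". In the general (non-organ-specific) part of Table 2, the surgeon has two columns, surgical difficulty and risk, and the anaesthetist has one, headed "Risk of complication (0 = no, 1 = yes"). The organ-specific part, "Targeted organ-specific factors impacting surgical difficulty and risk for complication (organ-specific scoring system) shown in an exemplary way for laparoscopic/robotic radical prostatectomy", has surgeon columns only.

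**The difficulty index.** In section 4.1 the "parameters and outcome measures will be determined by experienced high-volume surgeons (≥1000 major interventions and >10 yr of surgical experience) using the Delphi method". The outcomes are then named: "Primary outcome measures for surgical difficulty will include operation duration, blood loss and transfusion, use of haemostatic agents, and the surgeon’s judgement", the last on a scale of 0 to 100.

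**The concern.** A stated aim needs something in the plan that measures it. Two places in section 2.2 commit the study to an anaesthetic view of difficulty. The three places that define how difficulty is rated, who sets its parameters and what it is tested against give the task to surgeons.

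If the survey runs as section 3.2 and Table 2 describe, the Delphi rounds will produce no rating of what makes an operation harder for the anaesthetist. The database phase does not fill the gap, because section 4.1 names no outcome that reflects it. The part of Aim 4 concerning anaesthetists could not then be reported, and the difficulty index would rest on the surgeon's perspective although objective 3 says both are needed.

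**Working it through.** The protocol gives no figure to reproduce here. The check sets the aims against the instrument and asks, at each step, whether anything measures anaesthetic difficulty.

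| Place | Surgeon | Anaesthetist |
|---|---|---|
| Table 4, Aim 4 | difficulty promised (urologists) | difficulty promised |
| Section 2.2, objective 3 | perspective required | perspective required |
| Section 3.2 | difficulty and risk | risk |
| Table 2, general preoperative (14 named items) | difficulty and risk | risk |
| Table 2, general intraoperative (13 named items) | difficulty and risk | risk |
| Table 2, immediate postoperative (2 items) | risk | risk |
| Table 2, organ-specific example (12 + 13 items) | difficulty and risk | no column |
| Section 4.1, who sets difficulty parameters | high-volume surgeons | not named |
| Section 4.1, difficulty outcomes | operative measures, surgeon's judgement | none |

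**Size of the gap.** The rows that matter are those where anaesthetists already rate and surgeons already rate difficulty: 14 + 13 = 27 items. They include ventilation difficulties and ECG abnormalities, where an anaesthetist's view of difficulty is most obviously relevant. The 2 postoperative rows do not count, since surgeons have no difficulty column there either. The 12 + 13 = 25 organ-specific rows describe operative anatomy and tumour, and nothing suggests that anaesthetists should rate them.

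**Does any other text fill the gap?**
- Section 3.1 (survey Part 2) asks all participants for opinions on what influences surgical difficulty. That is general opinion, not a rating of each parameter, and it does not concern difficulty for the anaesthetist.
- Section 3.3 has experts, not split by discipline, score each factor from 0 to 10 in round 2. The scores are for risk and for surgical difficulty.
- Section 3.5 has both disciplines assign weights, separately for surgical difficulty and for complication risk, but makes the weighting depend on which discipline assesses the parameter. Under section 3.2, difficulty is assessed by surgeons.
- Section 3.2 also says that factors affecting the anaesthetist are rated by anaesthetists alone. It is speaking of risk factors, and the same paragraph ends by describing the anaesthetist's task as complication risk.

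These passages could let anaesthetists comment on surgical difficulty, which sits uneasily with the split in section 3.2. None provides an anaesthetic difficulty rating.

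**The case against.** The strongest reply is that the index is one of surgical difficulty throughout, and that section 4.1 says openly that surgeons determine it. Objective 3 asks for surgical complexity seen from two perspectives, which is not literally a request to rate anaesthetic difficulty. That is fair for objective 3 read alone. It does not cover Aim 4, which names anaesthetists as people for whom operations become more difficult, and even objective 3 needs some anaesthetic input on complexity that section 3.2 does not collect.

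The instrument is also not final. Table 2 is headed as proposed and has open rows for expert suggestions, two to five rounds are foreseen, the steering committee includes anaesthetists, and the supplementary tables are not shown. This means that the gap can still be closed. It does not close it: the open rows admit new parameters, not a new rating dimension, and the article's text, table and analysis section all agree on the split. The outcome list in section 4.1 is worded so that more could be added, but it names the surgeon's judgement with no anaesthetic counterpart.

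Four stronger readings are tempting, and the document does not support them:
- *Aim 4 as a whole cannot be answered.* The urologist half can be, from the surgeon columns.
- *The 20 anaesthetists among the minimum 50 panellists (20/50 = 40%) contribute nothing to the difficulty index.* The wording of sections 3.1, 3.3 and 3.5 is too loose to establish that.
- *Anaesthetic items will receive near-zero or uninformed difficulty weights.* Nothing in the document shows this.
- *The gap cannot be repaired once the survey starts.* Further rounds, or a return to the panel, remain possible.

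**Conclusion.** The mismatch holds in a limited form. The anaesthetist half of Aim 4, and the anaesthetic perspective that objective 3 calls necessary, have no matching rating in section 3.2 or Table 2 and no matching outcome in section 4.1. It affects 27 general items and one missing type of outcome. It does not touch the surgeon-rated difficulty index, the complication-risk ratings or the urologist half of Aim 4.

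The conclusion assumes that section 3.2 and Table 2 govern who rates what, and that the unseen survey and supplementary tables follow them. It should be resolved before round 1 opens, when both remedies are cheapest.

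**What to change.** Choose one of two routes.

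**Measure it.**
- In Table 2, add an anaesthetist-rated difficulty column for the 27 general pre- and intraoperative items, scored 0/1 in round 1 and 0 to 10 in round 2, in line with the scales already in use.
- In sections 3.2 and 3.5, say that anaesthetists rate difficulty for these items, and whether their weight is kept separate from the surgeon's difficulty weight or combined with it.
- In section 4.1, add a matching outcome, such as the anaesthetist's judgement of difficulty on 0 to 100 alongside the surgeon's. Without this, anaesthetic weights would enter an index tested only against operative measures and the surgeon's opinion.

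**Or narrow the aim.** Restrict Aim 4 and objective 3 to surgeon-rated surgical difficulty, and label the index so wherever it is reported.

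Under either route, align the general wording in sections 3.1, 3.3 and 3.5 with section 3.2, so that it is clear which discipline rates difficulty.

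The first route costs a few more survey minutes for each anaesthetist and one more judgement to record for each case in which the outcome is collected. The second costs only a narrower claim. Neither adds patients.
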